## Abstract

**Background:** Acupuncture has been clinically used to treat epilepsy after stroke. However, most of the current clinical studies are observational studies, and there are few well-designed randomized controlled trials (RCTs). Hence, we designed a multicentre RCT to assess the advantages and efficacy of acupuncture for post-stroke epilepsy (PSE).

**Methods/Design:** This is a two-arm, parallel, participants-blinded and assessor-blinded and multicentre RCT. A total of 120 patients with PSE aged from 18 to 75 years will be randomly assigned to two groups (routine treatment plus acupuncture group and routine treatment plus sham acupuncture group) at a 1:1 ratio. The participants will perform acupuncture or sham acupuncture treatment three times a week and be ongoing 8-week treatment. The primary endpoint is the proportion of seizure-free patients. A safety profile will be established. We will record adverse events for the safety evaluation.

**Discussion:** The study will provide high-quality clinical evidence on the effectiveness and safety of acupuncture for treating patients with epilepsy after stroke.

**Clinical Trial Registration:** Chinese Clinical Trial Registry, identifier: ChiCTR2100046114.

## Introduction

Stroke is a common cause of epilepsy in adults, causing about 10% of all epilepsy and 55% of newly diagnosed seizures in older adults (1). Although recent advances in the diagnosis and treatment of acute stroke have increased patient's life expectancy, the incidence of Post-stroke epilepsy (PSE) is also on the rise (1). PSE is defined as unprovoked epileptic seizures at least 1 week after stroke and occurs in at least 4-6% of the stroke patients (2). PSE is one of the major complications after stroke. A meta-analysis found that younger age, hemorrhagic component, and cortical involvement at stroke onset were associated with a higher risk of PSE (3). PSE may be associated with increased mortality and unfavorable outcomes. In addition, there is a high risk of seizure recurrence following an unprovoked seizure after a stroke. Although the European Stroke Organization guidelines recommend that treatment with antiepileptic drugs (AEDs) should be considered after one unprovoked seizure (4), there is currently limited evidence on the efficacy and safety of AEDs for PSE (1, 4, 5). The management of PSE is also challenged by several factors, such as the changes in pharmacodynamics due to older age, co-morbidities, and co-medications in stroke survivors. Older people, in particular, may be more susceptible to side effects from antiseizure medications (5).

As an essential part of traditional Chinese medicine (TCM), acupuncture has a history of more than 3,000 years in China and spread to Europe and American between the 16th and the 19th century. As one of the oldest medical approaches globally, acupuncture is a complementary medicine modality that involves inserting needles into specific parts of the body and then stimulating them by manual operation, electric pulses, or heat (6). Doctors and scientists have struggled to assess the actual effects of acupuncture and the underlying biological and physiological mechanisms of acupuncture. Clinical trials in different countries have shown that acupuncture may have beneficial effects on various diseases, including osteoarthritis, stroke, gastrointestinal disorders, cancer pain, and so on (7–11). Also, during the COVID-19 epidemic, TCM, including acupuncture, was widely used in treating COVID-19 patients, and acupuncture may have a positive effect on patients (12, 13). There has already evidence that acupuncture is feasible for treating movement disorders (14), as routine treatment has significant limitations. As a personalized treatment, acupuncture offers the potential to treat refractory epilepsy (15, 16). The imbalance between the sympathetic and parasympathetic activities may cause different diseases, and ultimately damage different brain regions. Researchers have found that acupuncture can not only activate the above-mentioned brain regions, but also relieving the autonomic nervous response by regulating the relevant adaptive neurotransmitters in distinct brain areas (16). Some experiments have investigated the mechanisms of action underlying acupuncture in treating epilepsy. An animal study shows that acupuncture can down-regulate C/EBP homologous protein expression and up-regulate glucose-regulated protein 78 protein expression level in epilepsy rats, which may be the protective effect of acupuncture on epileptic brain injury (17). Another animal study suggests that the effect of acupuncture on epileptic rats may be related with change of GAD (67) mRNA level in dentate gyrus region (18). The thalamus plays a crucial role in the sensory transmission and is closely related to the epilepsy genesis. Since the thalamus is a converging structure of acupuncture and vagus nerve stimulation, and the activity of thalamic neurons can be modulated by acupuncture, this may be one of the mechanisms of acupuncture in treating epilepsy (19). In 2018, Deng et al. (20) conducted a systematic review and meta-analysis, which detected that acupuncture therapy might have a positive effect in the treatment of epilepsy. However, the evidence was insufficient and limited due to the high risk of bias and the low quality of the included studies. A retrospective matched cohort study has shown that stroke participants who received acupuncture had a lower chance of epilepsy than those who did not. Nevertheless, whether acupuncture can be used for primary and secondary prevention of PSE needs to be further validated in prospective cohort trials (21).

Current evidence on the effects of acupuncture on epilepsy in stroke patients is insufficient. Now, we will use acupuncture as a clinical TCM rehabilitation method for PSE. Therefore, we hypothesize that acupuncture will have better clinical efficacy than sham acupuncture in clinical symptoms, cognitive function, and quality of life.

## Methods and Analysis

### Study Design

A multicentre randomized controlled trial (RCT) will be conducted at the Tianjin Nankai Hospital, Tianjin Rehabilitation and Convalescence Center of PLA, Tianjin Gong An Hospital, The Second Hospital Affiliated to Tianjin University of TCM, all of which are teaching hospitals. The protocol was registered with the China Clinical Trial Registry (item number: ChiCTR2100046114), and this study protocol has been approved by the Ethics Committee of Tianjin Gong An Hospital (item number: 2020003). A total of 120 participants will be recruited. All participants will provide written informed consent at the time of recruitment. PSE participants will be recruited and randomly assigned to either conventional therapy plus acupuncture or conventional therapy plus sham acupuncture. The evaluator will evaluate and analyze the results at four points (before treatment, 4 weeks, 8 weeks, and 1 year). Tianjin University of TCM will be responsible for data management and statistics. The flow chart of the trial is illustrated in Figure 1, and Table 1 shows the schedule of measurements.

**Figure 1 F1:**
[figure not shown]
Flow chart of the trial. DMC, data monitoring committee.

**Table 1 T1:** Study schedule showing the time points for enrollment and assessment.

**Period**	**Run-in period**	**Treatment period**		**Follow-up period**	
**Day**	**−7-0 days**	**0**	**4 weeks**	**8 weeks**	**1 year**
Informed consent	×	×			
Inclusion/exclusion criteria	×	×			
Medical history	×	×			
Medical examination	×	×			
Combined disease treatment	×	×			
**Outcomes**					
The proportion of seizure-free patients			×	×	×
The time recurrence to the first seizure			×	×	×
The proportion of completed diary entries			×	×	×
Mini-mental status examination		×	×	×	×
Montreal cognitive assessment		×	×	×	×
Activities of daily living		×	×	×	×
EEG assessment		×	×	×	×
**Safety**					
Adverse events		×	×	×	

*× represents the beginning of information collection*.

### Participant Recruitment

Epilepsy is diagnosed according to International League Against Epilepsy guidelines, and consequently, one unprovoked seizure occurring more than 1 week after stroke will be defined as PSE (22–24). Participants with a first post-episode of seizures a week after a stroke confirmed will be recruited. The PSE will be diagnosed following an examination, brain CT/MRI scan, and electroencephalogram (EEG) of participants. Recruitment advertisements will be posted on, the hospital websites, inpatient departments, WeChat, Facebook, Tik Tok, and other official platforms to recruit potential patients. The informed consent process will be conducted by the study coordinator or principal investigator, and if the participants agree to sign the informed consent, they will be screened to confirm that potential participants meet the eligibility criteria listed below.

### Inclusion Criteria

Participants with the following conditions will be included: (1) patients with PSE; (2) age range from 18 to 75 years old; (3) in stable condition and conscious; (4) no psychiatric drugs have been taken in 2 months; (5) the informed consent is signed by the participant or his/her immediate family; (6) regardless of whether the patient taking anticoagulant and/or antiplatelet therapy (25).

### Exclusion Criteria

Participants with the following conditions will be excluded: (1) a history of psychiatric disorders; (2) being pregnant or lactating; (3) a personal or family history of epilepsy; (4) central nervous system infection, traumatic brain injury, or intracranial tumor; (5) alcoholism, poisoning, cortical dysplasia, or other condition that may cause seizures; (6) suffering from psychogenic non-epileptic seizure by video-EEG evaluation (26).

### Randomization and Blinding

Randomization will be computer-generated by independent researchers using SAS 9.3 (SAS Institute Inc., Cary, NC, USA) software. Researchers will place the generated list of random numbers into sequentially numbered, opaque, sealed envelopes. Based on the information received from the envelope, consecutive participants will be randomly assigned in a 1:1 ratio to acupuncture group (AG) or sham acupuncture group (SAG). Acupuncturists will be appointed to perform the acupuncture for both groups separately. The research coordinator will not be involved in assessment or treatment. And they will notify the patients that they would be likely to receive either a “less-painful acupuncture developed especially for this study” (sham) or a “traditional Chinese acupuncture” (true). All patients and statisticians will be blinded to group assignments.

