### Statistical Analysis

The researchers of Tianjin University of TCM will perform statistical analysis, and they will analyze the data using SAS 9.3 software. Statistical analysis is conducted by researchers with statistical qualifications. Results data will be analyzed in accordance with the intent-to-treat principle, including all patients after baseline assessment, regardless of whether they received treatment or not. Statisticians will use descriptive statistics to summarize the demographic characteristics of the two groups. We will describe continuous variables in terms of mean and standard deviation, and use the *t*-test. Categorical variables will be undertaken using the χ2 test.

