## Discussion

Stroke is one of the major global health problems, and its disease burden continues to increase due to the increasing aging of the population. PSE is a common complication after stroke, and although many doctors prescribe AEDs as secondary prevention of PSE, evidence on the efficacy and safety of the drugs is still limited (39). Given the lack of clear evidence of drugs for PSE, complementary and alternative medicine may have a promising future in the treatment of PSE from this perspective. Acupuncture is a simple, effective, and safe complementary and alternative therapy for various diseases, including stroke and epilepsy (11, 40–45). Based on published systematic reviews, acupuncture seems to be a promising therapy for epilepsy (20, 46). However, few RCTs acupuncture treatment for PSE has been published.

We have carefully designed the current RCT to provide reliable evidence of the advantages and effects of acupuncture on PSE. Computer-generated randomization of numbers and allocation concealment will be used to minimize selection bias. The evaluators will be blinded to the group allocation. In addition, we set up a sham acupuncture group to solve the problem of the blinding method. In summary, we will conduct an RCT to test the efficacy of acupuncture in 120 patients diagnosed with PSE. We plan to publish our data in a high-profile emergency medicine or neurology journal. It certainly largely depends on the results of the research. We will do our best to discharge our administrative duties.

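### Four hospitals, but the only test named for seizure freedom is a χ2 with no hospital term: valid, but open to a cheap gain in precision

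*Protocol article*

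**What the plan says.** Study Design names four hospitals ("A multicentre randomized controlled trial (RCT) will be conducted") and sets the total: "A total of 120 participants will be recruited". At 1:1 that is 60 per arm.

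Randomization and Blinding describes a computer-generated sequence. "Researchers will place the generated list of random numbers into sequentially numbered, opaque, sealed envelopes", and from these "consecutive participants will be randomly assigned in a 1:1 ratio to acupuncture group (AG) or sham acupuncture group (SAG". The list is in the singular. Hospital, strata and blocks are not mentioned, either as used or as not used.

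The Abstract gives a binary primary endpoint: "The primary endpoint is the proportion of seizure-free patients". The Primary Outcome section words it as a second seizure under treatment, or completion of 12 months without one. That also classifies each patient in one of two ways.

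Statistical Analysis names two tests. Continuous variables get a t-test. For the rest, "Categorical variables will be undertaken using the χ2 test". Neither is given a hospital term or any other covariate.

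**The concern.** In a multicentre trial, hospital can predict outcome through case mix, drug management and completeness of follow-up. Interventions and Comparison has antiepileptic drugs fitted to each patient, with adjustment left to neurologists, so some difference between hospitals in seizure freedom is plausible. The article gives no figure for it.

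If hospital does predict outcome, a χ2 test without hospital has one of two weaknesses:

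- **One list across hospitals.** Arms can be unequal within a hospital by chance. The resulting difference in hospital mix stays in the treatment comparison as noise.
- **Lists stratified by hospital.** The mix is balanced, but the pooled χ2 variance still counts between-hospital variation that the design has removed. The test then rejects too rarely.

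What is at stake is power in a trial of 120, and protection against an awkward chance imbalance. The validity of the comparison is not at stake.

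**Working it through.** **The plan's own figure.** N = 120 cannot be reproduced, because the article gives no alpha, power or event rates. For scale, at an assumed two-sided 5% alpha, 60 per arm has 80% power for about 50% vs 75%, or 60% vs 83%.

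**Inputs.** From the article: four hospitals, 120 patients, 1:1, χ2 test. Assumed: 30 patients per hospital; control seizure-free rates of 60% in each, 45/55/65/75%, or 35/50/70/85% (mean 60% in every case); log odds ratio 1.18, which takes 60% to 83%.

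**Step 1: how uneven can a hospital be?** With independent 1:1 assignment, a hospital of 30 splits 20:10 or worse with probability P(X ≤ 10 or X ≥ 20) = 9.9%, where X ~ Binomial(30, 0.5). For at least one of four hospitals: 1 − (1 − 0.0987)^4 = 34%.

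**Step 2: how much noise does that add?** Let p̄ = 0.60, so p̄(1 − p̄) = 0.24. The mean within-hospital variance is W = Σ p_h(1 − p_h)/4.

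- 35–85%: W = (0.2275 + 0.25 + 0.21 + 0.1275)/4 = 0.2038. Between-hospital part: 0.24 − 0.2038 = 0.0362.
- 45–75%: W = (0.2475 + 0.2475 + 0.2275 + 0.1875)/4 = 0.2275. Between-hospital part: 0.0125.

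With one list of 60/60, the arm difference due to hospital mix alone has SD = √[between × (1/60 + 1/60) × 120/119]. This is 3.5 points at 35–85% and 2.0 points at 45–75%. The total SD is √(0.24 × 2/60) = 8.9 points, and the χ2 variance already contains the hospital part.

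**Step 3: size of the χ2 test after stratified allocation.** The true variance is proportional to W, but the test uses 0.24. The effective cut-off is 1.96/√(W/0.24).

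- 35–85%: 1.96/√0.849 = 2.127, two-sided tail 3.3%.
- 45–75%: 1.96/√0.948 = 2.013, two-sided tail 4.4%.

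**Step 4: simulation** (100,000 trials per cell; differences taken before rounding). The CMH statistic is Σ(x_h − E_h)/√ΣV_h, with E_h = a_h m_h/n_h and V_h = a_h(n_h − a_h)m_h(n_h − m_h)/[n_h²(n_h − 1)]. In hospital h, n_h is the number of patients, a_h the number on acupuncture, m_h the number seizure-free, and x_h the number who are both.

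| Control rates | Allocation | Type I: χ2 | Type I: CMH | Power: χ2 | Power: CMH | Change from test alone |
|---|---|---|---|---|---|---|
| 60% in each | one list | 5.2% | 5.0% | 81.6% | 79.9% | −1.7 |
| 60% in each | per hospital | 5.1% | 5.0% | 81.5% | 81.0% | −0.6 |
| 45–75% | one list | 5.3% | 5.1% | 78.5% | 78.4% | −0.1 |
| 45–75% | per hospital | 4.5% | 4.9% | 79.4% | 79.9% | +0.6 |
| 35–85% | one list | 5.1% | 5.1% | 72.4% | 75.9% | +3.6 |
| 35–85% | per hospital | 3.3% | 5.0% | 73.8% | 77.1% | +3.3 |

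Stratifying the list and changing the test together moves power from 72.4% to 77.1% at 35–85%, from 78.5% to 79.9% at 45–75%, and from 81.6% to 81.0% with no spread.

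**Step 5: unequal hospitals.** With sizes 60/30/20/10, one list and log odds ratio 1.15 (40,000 trials), changing the test alone moves power from 80.0% to 78.2% (equal rates), 81.9% to 81.1% (50–70%), 80.3% to 81.8% (40–80%) and 76.9% to 81.0% (30–90%). The χ2 type I error is 5.2–5.5%. The pattern is the same.

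**The case against.** The strongest reply is that nothing here is shown to be wrong.

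- **Silence on strata.** This is a condensed article. Strata, blocks and envelope series by hospital are commonly left to the full protocol. A reader might infer from the singular list that allocation is unstratified, but the text does not say so. This stands, and the point does not depend on it.
- **The analysis line is generic.** It follows the descriptive statistics, it does not exclude a hospital factor, and CMH is itself a χ2-type test. This stands in part. Even so, the χ2 is the only named test that fits a binary endpoint, and it is named without a hospital term.
- **The test is valid.** A reader might infer bias or an inflated false-positive rate from hospital imbalance. With one list the χ2 keeps about 5%, because chance imbalance is already part of its error. After stratified allocation it errs on the conservative side.
- **The spread is assumed.** A reader might infer that drugs are managed differently by each hospital. The article ties tailoring to patient characteristics, says that routine care is to be consistent across groups, and calls all four sites teaching hospitals. A range of 35–85% across four hospitals is wide.
- **The t-test.** It concerns continuous secondary outcomes and cannot affect the primary comparison.
- **A stratified test is not always better.** With no spread the plain χ2 is slightly ahead, so it cannot be said that the stated method loses in every case.

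What survives is narrower: a named method for the primary endpoint that ignores hospital, when a method that uses it costs little.

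**Conclusion.** The point holds as a cheap improvement to the stated analysis; it is not an error that invalidates the trial. Under either allocation scheme, a hospital-stratified or hospital-adjusted primary test would keep type I error near 5%. Under stratified allocation it would also remove the conservatism of the χ2 (about 3.3–3.4% at 35–85%, about 4.5% at 45–75%).

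The power effect of changing only the test runs from a gain of about 3 to 4 points with a wide hospital spread (35–85%), through about nothing at a moderate one (45–75%), to a loss of about 0.5 to 2 points if hospitals do not differ. These figures rest on assumed hospital rates, 30 patients per hospital, and an assumed log odds ratio of 1.18; the article supplies none of them. The documents do not support calling the allocation unstratified, the comparison biased, or the χ2 worse in all circumstances.

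**What to change.** 1. State whether the allocation list is stratified by hospital.
2. For seizure freedom, replace the χ2 with a CMH test stratified by hospital and report a common risk difference, or use logistic regression with hospital as a factor. Name one of these as primary.
3. Include hospital as a factor in the models for the continuous secondary outcomes (MMSE, MoCA, ADL).
4. If the list is not already stratified, generate a permuted-block list with varying block sizes for each hospital, and one envelope series per hospital, before the first patient. On the dates in Trial Status (protocol of May 2021, first participant December 2022) there is room for this. If enrolment has begun, items 1 to 3 can still be fixed before unblinding.

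The cost is one or two sentences of analysis text and, where needed, a new list. The statistical price is the 0.5 to 2 power points above if hospitals turn out alike. It is nearer 0.6 when the list is stratified too.

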### Interventions and Comparison

Both groups will receive routine stroke care and treatment during the whole 8-week study. The program was designed according to the Chinese Stroke Association Stroke Council Guideline will be consistent across groups (27). Chinese herbal medicine will be prohibited during the trial. The routine use of prophylactic anticonvulsant drugs for PSE remains largely controversial. Although many physicians use AEDs as secondary prevention of PSE, there is insufficient evidence on which AEDs are most effective in preventing recurrent epilepsy (1, 4, 5). The 2013 International League Against Epilepsy (ILAE) report suggested carbamazepine (CBZ), Levetiracetam (LEV), phenytoin (PHT) and zonisamide (ZNS) have “level A” evidence (28). Multicenter prospective RCT suggests that LEV in monotherapy is a safe and effective therapeutic option in elderly patients who have suffered PSE (29). So, we will use AEDs to prevent PSE recurrence. AEDs should be tailored to patients according to their age, type of seizure, drug interaction, physical health and other factors. Medication adjustment is handled by neurologists with more than 5 years of clinical experience. If participants present repeated, uncontrolled seizures, they should be given rescue medications that rapidly control the seizure, such as diazepam, midazolam propofol and so on, along with effective supportive treatment, symptomatic treatment, such as keeping the respiratory tract open, correcting acid-base balance, correcting electrolyte disturbances, and preventing or controlling infection (30).

We plan to start acupuncture at the beginning of treatment (together with the AEDs). Acupuncture treatment for the assigned participants will be performed by acupuncturists who have at least 5 years of clinical experience. The participants will receive 30 min of real or sham acupuncture sham acupuncture in a supine position, three times a week for eight weeks. To improve and monitor compliance, those who complete all treatments and assessments will receive financial compensation. Besides, each treatment form and evaluation form will be filled out and signed by patients and investigators.

